**Secondary safety endpoints**
• SaO_2_, PaO_2_ and PaCO_2_ at inclusion, 10 and 25 min after the start of Vent2Cool procedure and 1 h, 2 h, 12 h, 24 h, 48 h and 72 h after the end of procedure
• Occurrence of an episode of severe oxygen desaturation (SpO_2_ < 75%) on pulse oximeter lasting at least 5′ during the Vent2Cool procedure
• Occurrence of severe hypercapnia (PaCO_2_ > 75 mmHg); hyperoxemia (PaO_2_ > 400 mmHg); hypoxemia with PaO_2_ < 75 mmHg in arterial blood at t = 10 and 25 min after starting Vent2Cool procedure
• Occurrence of an episode of major systemic hypotension (invasive or non-invasive measurement) with systolic blood pressure < 60 mmHg during Vent2Cool procedure
• Heart rate measured from the EKG or blood pressure signal at 10 and 25 min after starting Vent2Cool procedure and at t = 1 h, 2 h, 12 h, 24 h, 48 h and 72 h after the procedure
• Systemic systolic and diastolic blood pressure at 10 and 25 min after starting Vent2Cool procedure and at t = 1 h, 2 h, 12 h, 24 h, 48 h and 72 h after the procedure
• Presence of arrhythmia or unexpected electrocardiographic abnormality
• Early termination of the Vent2Cool procedure before reaching a core target temperature below 33 ± 0.5 °C (failure of cooling induction)
• Number and percentage of patients for whom the core temperature has reached a value lower than 30 or 32 °C within 60 min after the start of the Vent2Cool procedure
• Adverse events related to Vent2Cool procedure, i.e., appearance of a perfluorothorax, unexpected cardiac arrhythmia or major hemodynamic instability, major hypoxemia during or immediately after the Vent2Cool procedure (i.e., during the first hour following the end of the procedure)
• Ventilatory parameters after the Vent2Cool procedure, i.e., measured values of positive end-expiratory pressure (PEEP), end-inspiratory pause pressure (Plateau pressure), driving pressure and static pulmonary compliance at t = 1 h, 2 h, 12 h, 24 h, 48 h and 72 h after the Vent2Cool procedure
• Occurrence of pulmonary infection in the ICU
• Presence or absence of pleural collection of perfluorocarbon in the lungs on thoracic computed tomography examination in patients surviving on Day 28 after cardiac arrest.

**Table 2 t0010:** Summary of the secondary endpoints for cooling performance, implementation in the care pathway, survival and neurological outcome, and clinical pathology.

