### Trial objectives

The primary objective is to demonstrate the ability of the Vent2Cool medical system (Orixha, Paris, France) to perform hypothermic TLV. Vent2Cool performance and efficacy have been rigorously validated *in vitro* and *in vivo*.^11^, ^12^, ^13^, ^14^, ^15^, ^16^ URTH targeted the achievement of core body temperature of 33.0 ± 0.5 °C within 60 min after the start of the procedure in patients resuscitated after intra- or extra-hospital cardiac arrest.

As secondary objectives, the study will aim at demonstrating: the safety of the procedure, the cooling performance, the ability to be implemented in the emergency setting of post-cardiac arrest management, clinical outcomes and impact on biological markers.

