**Fig. 1 f0005:**
[figure not shown]
Schematic representation of the study design. *ROSC, resumption of spontaneous circulation; TTM, target temperature management; mRS, modified Rankin Score.*

Once the inclusion process has been completed, the Vent2Cool system will be set up according to instruction for use, after installation of a single-use Breathing Circuit as well as a single-use bag containing sterile breathable liquid called “Liquid2Breathe”. Schematic illustrations and picture of the Vent2Cool system are illustrated in Fig. 2, Fig. 3, respectively. Prior to the beginning of the Vent2Cool procedure, the user will enter the Ideal Body Weight of the patient and confirm the pre-set parameters for end-expiratory liquid volume (EELqV), liquid tidal volume (Vt) and Fraction of oxygen in the gas mixture (FgO_2_). This is performed on the Vent2Cool touch screen in order to personalize the treatment (i.e. quantity of breathable liquid) for the given patient. The user will start the Vent2Cool procedure after disconnection of the endotracheal tube from the gas ventilator followed by a rapid secured connection to the Vent2Cool connector. Upon switching the Vent2Cool valve ON, the Vent2Cool system automatically fills the lungs with breathable liquid and starts URTH induction. Throughout the procedure, the user can modify EELqV (10–20 mg/kg IBW), Vt (6–9 ml/kg IBW) and the FgO_2_ (50–100%). Of note, FgO_2_ is fully distinct from the inhaled fraction of oxygen used in conventional ventilation as this is the fraction of oxygen in the gas mixture delivered by Vent2Cool into the breathable liquid, but not the fraction of in in the breathable liquid. The end of the procedure is expected to occur after reaching a core temperature of 33.0 °C and a procedure duration of less than 60 min. The investigator can stop the procedure at any moment for any safety reason. When stopping the procedure, the Vent2Cool system automatically withdraws the maximal amount of breathable liquids from the lung through a lung draining procedure. The user will end the Vent2Cool procedure by closing the patient connector valve a reconnecting the endotracheal tube to the gas ventilator. If required, the investigator will use bronchoscopy to suction residual amounts of breathable liquids. It will be suggested to maintain a Vt less than or equal to 6 ml/kg and a positive end-expiratory pressure (PEEP) of at least 5 cmH_2_0 for a minimum of 8 h following the procedure. The use of a heat and moisture exchanger (HME) on the respiratory circuit will be discouraged during this same period and the use of a heated humidifier should be favored.

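### The severe-desaturation endpoint stops counting when the procedure ends, so an episode with under 5 minutes on liquid that continues after reconnection is missed

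*Protocol article*

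**What the plan says.** Safety is a stated secondary objective: "the study will aim at demonstrating: the safety of the procedure" (Protocol article, Trial objectives). The only pulse-oximetry endpoint with a numeric limit is in Table 1: "Occurrence of an episode of severe oxygen desaturation (SpO_2_ < 75%) on pulse oximeter lasting at least 5′ during the Vent2Cool procedure".

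The window opens when the connector valve is opened (Primary and secondary endpoints). Its end is described under Study intervention and target temperature management: "The user will end the Vent2Cool procedure by closing the patient connector valve". That sentence goes on to name reconnection of the tube to the gas ventilator, so closure and reconnection together mark the end. When a stop is called, "the Vent2Cool system automatically withdraws the maximal amount of breathable liquids from the lung through a lung draining procedure", and this drainage comes before closure. The same section says: "The investigator can stop the procedure at any moment for any safety reason".

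Table 1 has other lines that bear on oxygenation. Blood gases are scheduled at inclusion, then "10 and 25 min after the start of Vent2Cool procedure and 1 h, 2 h, 12 h" and later, the post-procedure times running from the end. A line for related adverse events includes "major hypoxemia during or immediately after the Vent2Cool procedure" and defines the second part as the first hour after the end.

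**The concern.** The 5-minute minimum and the end of the window work against each other. The natural response to severe desaturation on liquid is to stop, drain and reconnect, and that response closes the window. A clinician who reacts quickly may end the procedure before 5 minutes have accrued, so the episode scores no event even if saturation stays below 75% on gas. A slower colleague with the same patient would have the event counted. The endpoint then reflects stopping behaviour as well as oxygenation.

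This is a first-in-human trial of total liquid ventilation with this device. The switch back to gas is a period of obvious interest, because liquid may remain in the lung and the article provides for bronchoscopic suction of it. An objective desaturation rate that leaves out part of that transition could look more favourable than the oximetry trace.

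**Working it through.** **Inputs.** Threshold 75%, minimum 5 minutes and window (Table 1); start of procedure (Primary and secondary endpoints); end of procedure, drainage and right to stop (Study intervention and target temperature management); 24 planned patients (Sample size and statistical analysis). The article gives no expected desaturation rate, drain time or typical procedure length beyond less than 60 minutes.

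**The plan's own figure.** There is none for this endpoint. The only computed figure is the Wilson 95% interval for 19/24 on the primary endpoint. It reproduces as 79.17% [59.53%; 90.76%], matching the stated 79.2% [59.5%; 90.8%]. The point does not depend on it.

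**Step 1: apply the rule to example episodes.** Let b be the minutes below 75% before the end of the procedure and a the minutes after it.
- Plain reading: count if b ≥ 5.
- Total-duration reading: count if b > 0 and b + a ≥ 5.
- Proposed rule: count if onset lies between valve opening and 1 hour after reconnection, and b + a ≥ 5.

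| b + a (min) | Total | Plain reading | Total-duration reading | Proposed rule |
|---|---|---|---|---|
| 3 + 4 | 7 | no | yes | yes |
| 4 + 4 | 8 | no | yes | yes |
| 3 + 3 | 6 | no | yes | yes |
| 5 + 2 | 7 | yes | yes | yes |
| 6 + 3 | 9 | yes | yes | yes |
| 0 + 8 | 8 | no | no | yes, shown as onset after reconnection |

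The miss is confined to b < 5. The 3 + 4 and 5 + 2 episodes both last 7 minutes, and only the second counts.

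**Step 2: effect of a safety stop.** Let r be the time from onset to the decision to stop and d the time to drain and close. Then b = r + d, and the episode is missed when r + d < 5 and r + d + a ≥ 5. The drain time is not in the document. Assuming 0 to 3 minutes:
- d = 0: missed if the decision comes within 5 − 0 = 5 minutes of onset.
- d = 3: missed if the decision comes within 5 − 3 = 2 minutes of onset.

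Drain minutes count towards the 5, so a long drain narrows the gap.

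**Step 3: can other lines recover the case?**
- *Blood gases.* For a procedure of D minutes, the gap between the 25-minute sample and the first post-procedure sample is (D + 60) − 25. Taking D = 25 to 60 as an assumed range, the gap is 60 to 95 minutes. At D = 25 the earlier sample coincides with the end; otherwise none is scheduled close to reconnection. The line with a PaO2 limit of 75 mmHg uses only the 10- and 25-minute samples.
- *Adverse-event line.* It covers the right hour, but the article gives it no saturation limit or minimum duration, and the event must be related to the procedure.

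**Step 4: size.** If onset were uniform over the procedure, the last 5 minutes would hold 5/D of onset times: 5/60 = 8.3% to 5/25 = 20.0%. This is a share of onset times under assumed onset and duration, not an estimate of missed episodes, because only episodes that also outlast the end are lost. On the scale of the trial, one reclassified patient is 1/24 = 4.2 percentage points. Moving from 0/24 to 1/24 raises the Wilson 95% upper limit from 13.8% to 20.2%.

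**The case against.** The strongest reply is that the transition is already covered. The adverse-event line spans the end of the procedure and uses the same hour that the fix adopts, and the primary endpoint requires the return to gas ventilation to be safe. Restricting the numeric line to the liquid phase is also a coherent choice, which the hypotension line shares. A rule for episodes that straddle the end could sit in the full protocol or the SAP, neither of which is shown.

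Much of this stands. A reader might infer that such a desaturation goes unrecorded in the trial; the document does not support that, since the adverse-event line may well capture it. What that line does not supply is a count under the same numeric rule. The word safe in the primary endpoint is not defined in the article, so it gives no desaturation rate either.

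A reader might also infer that every episode crossing reconnection is lost. That is wrong: 5 + 2 and 6 + 3 are counted. Nor does the window close at valve closure alone, since reconnection is named with it.

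The wording can further be read as an episode that occurs during the procedure and lasts 5 minutes overall. That reading would count 3 + 4. It is tenable but less natural, and two readings that give different counts from one trace are themselves a reason to settle the rule. The article states a threshold, a duration and a window, so the point concerns a stated rule and not only absent detail.

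**Conclusion.** The point holds in a limited form. On the plain reading, an episode of SpO2 below 75% that begins on liquid, has less than 5 minutes before closure and reconnection, and reaches 5 minutes only afterwards is not counted. A prompt safety stop makes this more likely. The adverse-event line may record the case but does not give the same objective rate.

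The undercount cannot be sized from the document. The 8% to 20% share of onset times rests on uniform onset and an assumed length of 25 to 60 minutes; it should not be quoted as a miss rate. The conclusion itself rests on reading the 5 minutes as falling inside the procedure and on no counting rule being set in a document not shown.

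This is a minor improvement to a descriptive secondary safety endpoint in a 24-patient single-arm pilot. A reader might infer that the success rate or the planned precision is in doubt; neither depends on this line.

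**What to change.** Reword the desaturation line in Table 1 to count any episode of SpO2 below 75% with a total duration of at least 5 minutes and onset from valve opening to 1 hour after reconnection, with duration running across the end of the procedure. Report episodes separately by onset: on liquid, or after reconnection. The 5-minute minimum stays, so the endpoint still measures sustained desaturation. The extra hour is the one the adverse-event line already uses, and the split keeps the liquid phase visible on its own.

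The cost is one reworded line and review of 1 additional hour of pulse oximetry per patient. The reported desaturation rate may rise, partly because episodes that begin after reconnection are now included; the split by onset lets a reader see how much comes from each phase.

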Here, we describe the design of a “first-in-human”, open-label, single-arm, non-comparative pilot clinical study, named **“***Lung-Conservative Liquid Ventilation for the Induction of Ultra-Rapid Cooling After Cardiac Arrest*” (OverCool), aiming at evaluating the performance and safety of ultra-rapid therapeutic hypothermia (URTH) induction by TLV.

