### Patients’ follow-up

After rewarming, patients will be followed according to the hospital practices. They could be weaned from the ventilator and extubated, according to the centers procedure with, e.g., PaO_2_ (arterial oxygen tension) / FiO_2_ (Inhaled oxygen) ratio > 200 mmHg, FiO_2_ < 50%, PEEP < 8 cmH_2_O, lack of vasopressor administration, cough reflex and respiratory rate / tidal ratio < 105. The previously mentioned secondary end-points will be monitored until Day 3 after cardiac arrest, as shown in Table 1, Table 2. We will collect the final cause of the initial of cardiac arrest, coronarography data (if available), results of other etiological examinations (e.g., brain CT-scan, chest CT-scan), electroencephalogram, time of rewarming and time of normothermia achievement.

Study will end by a last visit by the investigator 28 days after cardiac arrest (“face to face”). During this visit, the investigator will record the number of days under mechanical ventilation, the occurrence or not of weaning from mechanical ventilation, the number of days in intensive care unit (before transfer to another ward), the number of days before hospital discharge, the number of days alive and permanently out of hospital, in case of death, cause of death, the current treatments and dosages, body core temperature any delayed adverse effects that can be attributable to Vent2Cool. A chest-CT scan will be performed to evaluate the presence or nor pleural collection of PFOB.

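### Table 1's only general adverse-event item and the Day-28 record of delayed effects are both worded by relation to Vent2Cool, so some harms can escape the stated endpoints

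*Protocol article*

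**What the plan says.** The Introduction describes a first-in-human, "open-label, single-arm, non-comparative pilot clinical study". Trial objectives lists safety among the secondary aims: "As secondary objectives, the study will aim at demonstrating: the safety of the procedure".

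Table 1 (Primary and secondary endpoints) has one general adverse-event item: "Adverse events related to Vent2Cool procedure, i.e., appearance of a perfluorothorax, unexpected cardiac arrhythmia or major hemodynamic instability, major hypoxemia", with the time limit "during or immediately after the Vent2Cool procedure (i.e., during the first hour following the end of the procedure").

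Under Patients' follow-up, the Day-28 visit records "any delayed adverse effects that can be attributable to Vent2Cool".

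Other Table 1 items carry no condition on cause. Examples are "Occurrence of an episode of severe oxygen desaturation (SpO_2_ < 75%) on pulse oximeter lasting at least 5′ during the Vent2Cool procedure", "hypoxemia with PaO_2_ < 75 mmHg in arterial blood at t = 10 and 25 min after starting Vent2Cool procedure" and a hypotensive episode "with systolic blood pressure < 60 mmHg during Vent2Cool procedure". Also unconditional are hypercapnia and hyperoxemia, arrhythmia or ECG abnormality, early termination, core temperature below 32 or 30 °C, ventilatory parameters to 72 h, pulmonary infection in the ICU, and pleural perfluorocarbon on CT in Day-28 survivors. Table 2 adds vital status with cause of death.

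**The concern.** Patients just resuscitated from cardiac arrest can become unstable, arrhythmic or hypoxemic without any help from the device. Whether such an event is *related* is therefore open to dispute. In this trial the people deciding would know the treatment, and there is no comparator rate against which to check them.

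An endpoint defined by relatedness makes the reported rate depend on that decision. It also yields a rate that later studies cannot easily compare with their own. What is at stake is the completeness of the safety description in a first-in-human study that sets out to demonstrate safety. The primary endpoint and the sample size are not affected.

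**Working it through.** **1. The plan's own figure.** The only statistical result in the article is the Wilson interval for 19 successes in 24 (Sample size and statistical analysis). With p = 19/24 = 0.7917, n = 24, z = 1.96:

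- centre = (p + z²/2n) / (1 + z²/n) = (0.7917 + 0.0800) / 1.1601 = 0.7514
- half-width = z·√(p(1−p)/n + z²/4n²) / (1 + z²/n) = 1.96 × √(0.00687 + 0.00167) / 1.1601 = 0.1561
- interval = 59.5% to 90.8%, as stated.

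It concerns procedural success. No figure in the article depends on the adverse-event item.

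**2. Two readings of the Table 1 item.**

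- *Related* as a judgement: an event enters only if it is attributed to the procedure.
- The list after *i.e.* as a definition: any event of a listed type in the window counts, with no judgement. The item is then closed, and it ends one hour after the procedure if the time limit governs the whole list.

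The Day-28 wording depends on attribution under either reading.

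**3. What each kind of harm can enter through.**

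| Harm | Item without attribution | What is left |
|---|---|---|
| Desaturation or hypotension during the procedure | Yes, by threshold | Nothing material |
| Arrhythmia, pulmonary infection, death | Yes | Nothing material |
| Pleural perfluorocarbon | CT in Day-28 survivors | Patients who die earlier: only the perfluorothorax entry in the general item |
| Hypotension or desaturation in the hour after the procedure | Only the sampled 1 h values | Episodes between samples: the general item only |
| Pneumothorax | None named | First reading: if attributed. Second: not listed |
| Other unlisted events (e.g. airway events, bleeding) | None named | Same as pneumothorax |
| Delayed non-fatal harm without its own item | None named | Day-28 item, if attributable |

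The post-procedure hour differs by reading. Under the first, an episode counts if attributed. Under the second, it counts without attribution, but only if *major*, which the item does not quantify.

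Pneumothorax matters because the Discussion reports that its risk rose with partial liquid ventilation and that this halted further research. The CT item looks for perfluorocarbon, which is a different finding.

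**4. Size per patient.** One patient reclassified moves the rate by 1/24 = 4.2 percentage points, up or down.

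**5. Illustration with assumed counts.** Suppose 8 of 24 patients have a qualifying event of any cause: 33.3% (Wilson 95% CI 18.0% to 53.3%). The reported rate then depends on the share judged related:

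- 25%: 2/24 = 8.3% (2.3% to 25.8%)
- 50%: 4/24 = 16.7% (6.7% to 35.9%)
- 75%: 6/24 = 25.0% (12.0% to 44.9%)

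**6. Illustration with assumed true rates, under-attribution only.** Let the device cause an event in a proportion π of patients, of which a fraction m is attributed to the arrest. The count is then binomial with n = 24 and probability π(1−m).

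- π = 20%: the chance of at most one counted event is 0.033 at m = 0, 0.292 at m = 0.5 and 0.661 at m = 0.75. Expected counts are 4.8, 2.4 and 1.2.
- π = 10%: the chance of no counted event is 0.080 at m = 0 and 0.292 at m = 0.5.

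This ignores the opposite error, and it ignores the items that would catch some of these events without attribution.

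**The case against.** Most of the obvious harms are already counted without attribution. A reader might infer that the trial's whole harm rate rests on attribution. Tables 1 and 2 do not support that: arrhythmia, pulmonary infection and death carry no such condition, and desaturation, abnormal blood gases and low pressure during the procedure are counted by threshold. This stands, and it confines the point to the gaps listed above.

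The list after *i.e.* may be a definition with no judgement step. This also stands as a possible reading. It removes the attribution problem from the Table 1 item but leaves a closed list, and it does not touch the Day-28 wording.

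The article is condensed. Full adverse-event recording and causality rules normally sit in the full protocol, so one may not infer that other adverse events go unrecorded. That is right, and no such claim is made. The point concerns how the article words an endpoint and a visit item; wider collection elsewhere would not change what that endpoint counts.

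A reader might also infer that the filter can only lower the count. The documents do not show this: unblinded staff using a new device may also blame it for events due to the arrest. The illustrative rates and shares are assumptions, not estimates.

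Finally, the Discussion links pneumothorax to the way gas was delivered in partial liquid ventilation and expects total liquid ventilation to be safer. That is a reason to expect fewer cases. It is no reason to leave the event unnamed in a study meant to confirm safety.

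**Conclusion.** The point holds in a limited form and should be acted on. The general adverse-event item is either conditional on an attribution that nothing in the design can check, or a closed list with a short window. The Day-28 item is conditional on attribution in any case. The stated endpoints can therefore miss pneumothorax, other unlisted events and delayed non-fatal harm. Between-sample episodes in the hour after the procedure depend on the general item alone.

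The direction of any bias is unknown. The only size that follows from the document itself is 4.2 percentage points per reclassified patient at n = 24; every other figure above rests on assumed rates. The conclusion takes the article's endpoint wording as the wording that will be analysed, and takes the time limit to cover the whole list.

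**What to change.** In Table 1, restate the item as all adverse events and all serious adverse events from valve opening to Day 28, regardless of judged relation to the device, as number and percentage of treated patients. Show events judged related, and the named procedural events with pneumothorax added, as subsets of that table.

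Under Patients' follow-up, have the Day-28 visit record all adverse events since the last assessment, with attribution as a separate field.

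The cost is endpoint wording and one additional table; no existing endpoint is lost. The headline count will be higher and will include events due to the arrest. Without a control arm the all-cause count still does not isolate device harm, and the report should say so.

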### Sample size and statistical analysis

The analyses will be conducted on the following patient sets: Safety population (SAF), Full Analysis Set (FAS) and Population Per Protocol (PP). The SAF includes all included and patients treated by Vent2Cool. The FAS (according to the Intent-to-Treat (ITT) principle) includes all treated patients, who had one post-baseline evaluation. The PP population includes all patients of the FAS except those with any major protocol deviation, that might significantly affect the completeness, accuracy, and/or reliability of the study data. The main endpoint analysis and secondary endpoint analyses will be based on the Full Analysis Set. A supportive analysis will be based on the Per Protocol population if more than 10% of patients are excluded from FAS.

A summary table and a flow chart will be presented for each patient population presenting the number of patients at each assessment and identifying the number of patients who withdrew over time, with the reason of premature study termination. Patients may withdraw from the study at any time, with or without reason and without prejudice to further treatment. Data that have already been collected on prematurely withdrawn patients will be retained and used for analysis, but no new data will be collected after withdrawal. Patients lost to follow-up, after hospital discharge before the end of the study, will be replaced. Data collected until the last available visit of these patients will be analyzed.

Based on an estimated success rate of around 80%, a sample of 24 analyzable patients was calculated as required to achieve sufficient precision of the success rate using Wilson's score interval, with a 95% confidence interval. Specifically, 19 of the 24 patients will have to undergo the procedure successfully, giving an expected success rate of 79.2% (95% CI [59.5%; 90.8%]).

Quantitative parameters will be described using the following summary descriptive statistics: number of patients, mean, standard deviation, median, first and third quartiles, and minimum and maximum values. Mean and standard deviation values will be reported to one decimal place greater than the data were collected. Median, first and third quartiles, minimum and maximum values will be reported with the same precision, as they were collected. Qualitative parameters will be described using frequencies and percentages.

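### Pleural perfluorocarbon is looked for systematically only on the Day-28 CT in survivors, so a collection found more than an hour after the procedure in a patient who later dies may fall outside both Table 1 endpoints

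*Protocol article*

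**What the plan says.** Two items in Table 1 (secondary safety endpoints) of the protocol article concern perfluorocarbon in the pleura.

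- **CT endpoint.** Presence or absence of a collection is determined "on thoracic computed tomography examination in patients surviving on Day 28 after cardiac arrest". The section on patients' follow-up places this scan at the last visit, 28 days after the arrest: "A chest-CT scan will be performed to evaluate the presence or nor pleural collection of PFOB".
- **Adverse-event endpoint.** The item begins "Adverse events related to Vent2Cool procedure, i.e., appearance of a perfluorothorax, unexpected cardiac arrhythmia or major hemodynamic instability" and goes on to major hypoxaemia. It closes with a time limit covering the procedure and the period immediately after it, explained as "i.e., during the first hour following the end of the procedure". It carries no survival condition.

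The follow-up section adds two further records. One is the etiological work-up, "results of other etiological examinations (e.g., brain CT-scan, chest CT-scan". The other, at the Day-28 visit, covers cause of death and late harms that could be due to the device.

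On populations, the section on sample size and statistical analysis states "The SAF includes all included and patients treated by Vent2Cool" and "The main endpoint analysis and secondary endpoint analyses will be based on the Full Analysis Set". The article describes no other systematic chest imaging for perfluorocarbon after the procedure.

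**The concern.** This is a first-in-human study. Safety is among its secondary objectives, and its conclusions speak of demonstrating safety in resuscitated patients generally. The Discussion itself recalls that an earlier trial of partial liquid ventilation found more pneumothorax, so pleural complications deserve a clear count.

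As worded, the protocol scan reaches only those alive at Day 28. The adverse-event item might have covered the others, but its window is unclear. A patient could have a collection found on day 2, die on day 6, and appear in neither listed endpoint. A report of no collections on CT would then describe survivors only, while a reader could take it as a statement about everyone treated. One late scan also shows only what is still present at Day 28.

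**Working it through.** **1. Coverage, item by item**

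| When a collection is found | Alive at Day 28 | Dies before Day 28 |
|---|---|---|
| During the procedure or within 1 h | Adverse-event item; CT if still present | Adverse-event item |
| After 1 h, time limit applied to the whole list | CT if still present | Neither Table 1 item; only the general record of late harms and cause of death |
| After 1 h, time limit applied only to hypoxaemia | Adverse-event item; CT if still present | Adverse-event item, with no stated end and no protocol imaging |

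The time limit follows directly on hypoxaemia, the last item in the list, so the grammar allows both readings. The gap in the middle row exists under one reading. Under the other, detection in patients who die depends on imaging done for other reasons, whereas survivors receive a protocol scan.

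**2. The plan's own figure**

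The plan gives no figure for this endpoint. Its only interval is the Wilson interval for the primary endpoint, 19/24. With p = 0.7917, z² = 3.8415 and n = 24:

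- centre = (p + z²/2n)/(1 + z²/n) = 0.8717/1.1601 = 0.7514
- half-width = z·√[p(1−p)/n + z²/4n²]/(1 + z²/n) = 0.1811/1.1601 = 0.1561
- interval = 59.5% to 90.8%, as stated

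That figure is correct and does not bear on this point.

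**3. How many patients the CT would cover**

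Inputs: 24 patients (sample size section). Day-28 survival is not given, so 30% to 70% is assumed. With zero collections seen among n scanned, the exact upper 95% limit is 1 − 0.025^(1/n) and the Wilson limit is z²/(n + z²). The last column is 1 − 0.9^n, the chance of at least one case if the true rate were 10% (an assumed value).

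| Assumed survival | n scanned | Exact upper limit | Wilson upper limit | Chance of at least 1 case |
|---|---|---|---|---|
| 30% | 7 | 41.0% | 35.4% | 52% |
| 50% | 12 | 26.5% | 24.2% | 72% |
| 60% | 14 | 23.2% | 21.5% | 77% |
| 70% | 17 | 19.5% | 18.4% | 83% |
| All assessed | 24 | 14.2% | 13.8% | 92% |

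**4. Does the survivor rate understate the rate in all treated patients?**

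Let p be the rate in all treated patients, s survival, and RR the ratio of mortality with a collection to mortality without one. Then d0 = (1 − s)/(p·RR + 1 − p), d1 = RR·d0, and the rate in survivors = p(1 − d1)/s. Take s = 0.5 and p = 0.20, both assumed:

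- RR 1.0: 20.0%
- RR 1.3: d0 = 0.5/1.06 = 0.472, d1 = 0.613, rate = 0.20 × 0.387/0.5 = 15.5%
- RR 1.5: d0 = 0.5/1.10 = 0.455, d1 = 0.682, rate = 12.7%
- RR 0.7: d0 = 0.5/0.94 = 0.532, d1 = 0.372, rate = 25.1%

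The sign of the difference depends wholly on RR, which the documents do not supply.

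**The case against.** The best defence is that the endpoint names its own population. For Day-28 survivors the restriction introduces no bias, and a careful reader will not carry the rate over to all treated patients. This stands, and it limits the point to what the trial can say beyond survivors.

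Three stronger conclusions are tempting, and the documents support none of them.

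- **That collections go unmeasured in patients who die.** The adverse-event item has no survival condition, its one-hour limit may apply only to hypoxaemia, and the follow-up section also records cause of death and late device-related harms. The full protocol may contain wider adverse-event reporting. What can be said is that these patients are not systematically imaged and that the listed endpoints may miss a late finding.
- **That the CT rate is too low.** This needs collections to go with higher mortality. It is plausible but not shown.
- **That pleural collection is the principal device harm.** The article lists several harms and does not rank them.

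Nor can the chest CTs already collected be assumed to fill the gap. They belong to the search for the cause of the arrest, may precede the procedure, and are not said to look for perfluorocarbon.

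Finally, counting all treated patients without imaging more of them would itself push the figure down if unimaged patients were scored as free of a collection. That is right, and the fix has to deal with it.

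**Conclusion.** The concern holds as a gap in endpoint definition and denominator. Systematic imaging for pleural perfluorocarbon is confined to Day-28 survivors. Under one natural reading of Table 1, a collection found between one hour after the procedure and a death before Day 28 belongs to neither listed endpoint.

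If survival is 30% to 70%, the CT result rests on about 7 to 17 of 24 patients, and zero findings would be compatible with rates up to 41.0% or 19.5% respectively (exact limits). Those limits concern survivors and depend on the assumed survival. The 14.2% limit for 24 patients applies only if all 24 are assessed, so it is a reference value and not a gain that rewording can deliver.

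No direction of bias is claimed. The matter is worth correcting because it decides which events the safety endpoint counts and whether the trial can say anything about pleural collections in all treated patients.

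**What to change.** Define the perfluorothorax endpoint in the safety population as any pleural perfluorocarbon collection found from procedure start to death or Day 28, whether on post-procedure chest imaging done for care or on the Day-28 CT. State that the one-hour limit does not apply to it. Because secondary endpoints are otherwise assigned to the Full Analysis Set, name the safety population explicitly for this one.

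For reporting:

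- Give cases over all treated patients, together with the number imaged at least once after the procedure.
- Treat patients with no post-procedure chest imaging as unknown, not as negative.
- Report the Day-28 CT separately as a survivor-only result, with number scanned over number treated.
- Keep chest CTs done before the procedure out of the count, which requires the imaging date and time.

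The cost is a change of endpoint wording and a few case report form fields (imaging done, date and time, collection yes or no), with no added imaging. The drawback is that imaging done for care is uneven between patients. The all-treated figure is therefore a minimum count, not an unbiased rate, and it does not have the precision of 24 imaged patients. The report should say so.
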